**FIGURE 1 clc23702-fig-0001:**
[figure not shown]
Schematic illustration of cohorts ASA, acetylsalicylic acid; MI, myocardial infarction. a Treated with a P2Y12 inhibitor (clopidogrel, prasugrel, ticagrelor 90 mg, or ticlopidine) ≤12 months prior to the ticagrelor 60 mg prescription. b ASA analyses will only be done when data available

### Data sources

2.3

To obtain a large and geographically diverse population, data will be extracted from data sources in the US and several European countries (Germany, Italy, Sweden, and the UK). Table 3 presents detailed information on each database, along with projected numbers of patients initiating ticagrelor 60 mg ≥1 year after their most recent MI available at the time of data extraction. In general, the study will use data on inpatient and outpatient care, prescriptions, and mortality when available. An estimated total of 7250 patients prescribed ticagrelor 60 mg are expected to be included across databases.

**TABLE 3 clc23702-tbl-0003:** Description of databases in each country

Country	Database(s)	Number of unique patients and National coverage (approximate)	Projected number of patients at time of data extraction^a^
US	Optum Clinformatics® administrative claims database combines data from over 50 healthcare providers in the US (>700 hospitals and 7000 clinics). The database provides a single‐payer view of data on demographics, diagnoses, and procedures performed during outpatient visits (outpatient specialist and physician visits) or inpatient stays, and outpatient prescription records (i.e., date of dispensed prescriptions). As is typical for US commercial claims databases, comprehensive data on mortality is not available in the Optum Clinformatics database.	180 million; 55%	750
	IBM's MarketScan Commercial Claims and Medicare Supplemental database consists of administrative claims submitted from US inpatient and outpatient encounters, as well as pharmacy claims (i.e., date of dispensed prescriptions). Medical claims are linked to outpatient prescription drug claims and person‐level enrollment information. The MarketScan supplemental database profiles the healthcare experience of retirees with Medicare supplemental insurance paid by employers. The Medicare Supplemental database provides data on medical and pharmacy claims for healthcare services performed in both inpatient and outpatient settings (i.e., date of dispensed prescriptions). As is typical for US commercial claims databases, comprehensive data on mortality is not available in the MarketScan database.	203 million; 62%	1200
	Medicare health insurance database covers fee‐for‐service claims data of individuals who are aged ≥65 years, select individuals with disabilities aged <65 years, and those with end‐stage renal disease. The data cover beneficiaries' encounters with the healthcare system and receipt of therapeutic interventions, including medications (i.e., date of dispensed prescriptions), procedures, and services. Data on mortality are available.	62 million; 19%	3100
UK	CPRD GOLD contains longitudinal primary care data from over 800 general practices, whereas CRPD Aurum holds anonymized, longitudinal, primary care patient records collected from over 1100 general practices. Data includes information on patient characteristics and issued prescription medicines. HES covers data on diagnoses and procedures for all hospitalization episodes from England, whereas ONS covers information on all‐cause and cause‐specific death. Data from both HES and ONS will be linked to primary care data of the CPRD. After removal of duplicates, GOLD and Aurum primary care databases will be used for the analysis.	13.5 million; 24% (GOLD+Aurum)	250
Sweden	The National Patient Register includes information on hospital discharge diagnoses and procedures. The Swedish Prescribed Drug Register covers data on all prescribed medications purchased at Swedish community pharmacies. The Cause of Death Register includes information on date and cause of death. The registers are linked by the register holder via the unique personal identification number.	10 million; >99%	800
Germany	AOK PLUS covers longitudinal claims data submitted from primary, secondary, and tertiary care, and contains information on patient demographics, inpatient hospitalizations, outpatient visits, procedures, mortality (inpatient and outpatient date of death), and outpatient prescriptions dispensed in pharmacies.	3.5 million; 4%	150
Italy	ReS database includes data on patient demographics, pharmacy‐dispensed prescription drugs, inpatient diagnoses and procedures, and date of in‐hospital mortality. For deaths in the outpatient setting, neither date of death nor cause of death is recorded in ReS.	5.5 million; 10%	1000
**Total estimated number of patients included across databases** ^a^			**7250**

Abbreviations: AOK, Allgemeine Ortskrankenkasse; CPRD, Clinical Practice Research Datalink; HES, hospital episode statistics; IBM, International Business Machines; MI, myocardial infarction; ONS, Office for National Statistics; ReS, Ricerca e Salute; Italian Research and Health Foundation; UK, United Kingdom; US, United States.

^a^
Projected approximate numbers of patients initiating ticagrelor 60 mg ≥1 year after their most recent MI, expected to be available in the data sources at the time of data extraction.

### Definition of treatment exposure and persistence

2.4

Treatment persistence for ticagrelor 60 mg will be defined as time on continuous treatment. To account for potential stockpiling, overlapping prescriptions will be assumed to be used sequentially. The treatment episode will be considered as continuous if the gap between days with available medication supply (grace period) is less than two times the number of days' supply of the most recent prescription. Patients with no further evidence of treatment before the end of the grace period will be defined as having discontinued treatment. The discontinuation date is defined as the date of the last prescription plus the number of days' supply in that last prescription plus 7 days, or the date of switch, or the date of death, whichever occurs first.

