The primary outcomes analyses will be based on an on‐treatment approach, censoring at treatment discontinuation. Additionally, an intention‐to‐treat approach will be used as a sensitivity analysis for the primary bleeding outcome and the secondary CV composite outcome. Sensitivity analyses will also be performed using two alternative definitions of treatment discontinuation, where the grace period is defined as 60 days in all databases, or where the discontinuation date is defined as the date of the last prescription of ticagrelor 60 mg plus half the number of days' supply in that last prescription plus 7 days.

Meta‐analyses will be applied to combine estimates derived from each country/database. Each meta‐analysis will be preceded by an assessment of heterogeneity in terms of patient characteristics and estimates. Heterogeneity will be quantified by the *I*
^2^‐statistic,^19^ and reasons for any observed heterogeneity will be explored prior to estimating the components of the meta‐analysis. A fixed‐effects approach will be used as the main method; random‐effects analyses will also be performed. The meta‐analysis results will be presented in Forest plots displaying the individual database‐level estimates with corresponding 95% CIs.

Regression models combined in the meta‐analyses will use predefined sets of covariates. These covariates will be selected based on the results of the country‐level regression models and clinical knowledge.

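### On-treatment time counts supply-gap days only when a refill follows, so on-treatment mortality is understated, and bleeding too if a bleed in a gap reduces refilling

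*Protocol article*

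**What the plan says.** Section 2.4 (Definition of treatment exposure and persistence) sets three rules.

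- **Bridging.** "The treatment episode will be considered as continuous if the gap between days with available medication supply (grace period) is less than two times". This multiple applies to the length of the latest supply.
- **Stopping.** "Patients with no further evidence of treatment before the end of the grace period will be defined as having discontinued treatment". Their end date is "the date of the last prescription plus the number of days' supply in that last prescription plus 7 days", or the switch or death date if earlier.
- **Stockpiling.** "To account for potential stockpiling, overlapping prescriptions will be assumed to be used sequentially".

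Section 2.7 (Statistical analyses) censors the main outcome analyses at that discontinuation date. It adds an intention-to-treat analysis for the primary bleeding outcome and the CV composite, and two alternative discontinuation definitions. One is "where the grace period is defined as 60 days in all databases"; the other ends exposure at half the last supply plus 7 days. The Discussion, in its sixth limitation, accepts that censoring at discontinuation may be informative. It offers intention-to-treat rates and a look at baseline predictors of discontinuation.

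**The concern.** Whether day 8 or later of an uncovered gap is on treatment depends on what happens afterwards. A patient who survives and refills contributes the whole gap. A patient who dies on day 20 of an identical gap never refills, so follow-up is cut back to day 7 and the death is lost. The later days enter the denominator but can never contain a death: this is immortal time. A bleed, MI or stroke in the same window is lost only when no refill follows it.

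The rule sets numerator and denominator for the primary bleeding outcome and the CV composite, and it feeds the 5000 person-year threshold. An error towards lower event rates is the unwelcome direction in a study meant to guide patient selection.

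The stockpiling rule also does not match the end date. Overlapping fills are used one after another, yet the end date as worded takes only the last prescription's own date and supply.

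**Working it through.** **1. The plan's own figure.** Section 2.8 assumes 0.5 bleeds per 100 person-years over 5000 person-years, i.e. 25 events. The Wald interval is (25 ± 1.96 × √25)/5000 = 15.2/5000 to 34.8/5000, or 0.304 to 0.696 per 100. The stated 0.3–0.7 reproduces. The article gives no figure for gap days.

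**2. Size of the bias, by algebra.** Let g be the share of counted time made up of bridged gap days beyond day 7, and q the probability that an event in such a gap prevents the refill.

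- Death: observed/true ≈ 1 − g.
- Bleeding, MI or stroke: observed/true ≈ 1 − g × q.
- CV composite, with w the share of its events that are deaths: observed/true ≈ 1 − g × [w + (1 − w) × q].

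**3. How long a bridged gap can be.** Just under 2 × 30 = 60 days, or 2 × 90 = 180 days. In the longest allowed refill interval, days beyond day 7 make up (60 − 7)/90 = 59% or (180 − 7)/270 = 64%. These are ceilings for one interval, not averages.

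**4. Simulation.** All inputs are assumptions except the bleeding rate of 0.5, which is the plan's. There were 400,000 patients, constant hazards whether or not supply was in hand, true death rate 2.0 per 100 person-years, and late refills with gaps uniform up to twice the supply.

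| Supply | Late refills | g | Death | Bleeding, q = 1 | Bleeding, q = 0.5 |
|---|---|---|---|---|---|
| 30 d | 10% | 0.069 | 1.847–1.861 | 0.465 | 0.477 |
| 30 d | 20% | 0.127–0.128 | 1.711–1.725 | 0.434 | 0.465 |
| 30 d | 40% | 0.219 | 1.549–1.550 | 0.388 | 0.438 |
| 90 d | 10% | 0.076 | 1.828–1.838 | 0.468 | 0.482 |
| 90 d | 20% | 0.140–0.141 | 1.706–1.720 | 0.419 | 0.463 |
| 90 d | 40% | 0.244 | 1.517–1.518 | 0.376 | 0.426 |

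With q = 0 and 20% late refills, bleeding is 0.505 (30 d) and 0.495 (90 d), so there is no bias. A separate run with milder gaps (600,000 patients, true death 3.0, true bleeding 1.0, 80% of bleeders stopping) had gap shares of 2%, 6%, 8% and 10%. It gave death 2.96, 2.78, 2.74 and 2.71, and bleeding 0.99, 0.94, 0.93 and 0.90.

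**5. Symmetric rules, 20% late refills, q = 1.** Counting supply + 7 days for everyone, with re-entry at the refill, gives death 2.018 and 2.015 and bleeding 0.501 and 0.490 (30 d and 90 d). Following everyone through the full grace period gives death 1.994 and 1.986 and bleeding 0.499 and 0.518. Both recover the truth within simulation error.

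**6. Planned sensitivity analyses.**

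- 60-day grace: identical to the main rule at a 30-day supply, since 2 × 30 = 60. At a 90-day supply, with gaps drawn up to 60 days, g falls to 0.045 and death is 1.917.
- Half supply + 7 days: non-refillers are cut at day 15 + 7 = 22 (30 d) or 45 + 7 = 52 (90 d), while refillers keep every day. Even with perfectly timed refills, 8/30 = 27% or 38/90 = 42% of each completed interval then counts only if a refill follows.
- Intention-to-treat: no conditioning on refills, but it estimates a different quantity.

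**7. Person-year threshold.** At g = 0.127 to 0.14, bridged days beyond day 7 would supply 635 to 700 of 5000 person-years.

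**8. Carry-over.** Three 90-day refills each 5 days early leave 3 × 5 = 15 days in hand; eleven 30-day refills each 2 days early leave 11 × 2 = 22. As worded, the end date omits them.

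**The case against.** The strongest reply is that the primary outcome is not shown to be biased. That is right as far as it goes: bleeding is affected only if q is above zero, and the documents say nothing about q. A reader might infer that all on-treatment rates are necessarily too low, but only death follows from the rule itself.

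Second, the size rests on assumed refill behaviour. In the milder run, a plan rate of 0.5 would fall only to between 0.495 and 0.45, small against an interval of 0.3–0.7. This stands as a limit on any claim of size. It also means that the data would not reveal the bias, and the bias does not shrink as databases are pooled.

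Third, the plan acknowledges informative censoring and includes an intention-to-treat analysis. That is a real safeguard, but it does not repair the on-treatment estimate. Baseline predictors of discontinuation cannot detect time that is conditional on a later refill.

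Fourth, sequential use may be meant to shift the last prescription's start, with the derivation given in the full protocol. That is possible, though the article's wording does not say it. A reader might also infer that dropped stock biases the rates. At a final stop, however, time and events are lost together. Rates would be affected only where stock in hand delays the next fill past supply + 7 days, and the documents give no fill patterns from which to judge that.

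**Conclusion.** The concern holds in a limited form. The stated rule makes exposure depend on a later refill, so on-treatment all-cause mortality, and the mortality part of the CV composite, is biased downward by about the gap share. For hospitalized bleeding, MI and stroke the bias is that share multiplied by the probability that an event in a gap prevents the refill, which may be zero. The documents fix neither quantity. For assumed gap shares of about 2% to 24%, death is understated by about 1% to 24%, and bleeding by between nothing and about as much. Of the planned alternatives, the 60-day grace period helps only where supplies exceed 30 days, and the half-supply date makes the asymmetry worse. The end-date wording is a separate and smaller fault that mainly shortens persistence and person-time.

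**What to change.** For event rates, apply one end-of-exposure rule whether or not a refill follows. One option is to follow everyone to the end of sequentially used supply + 7 days, at the first run-out not refilled within that time, with a sensitivity analysis that follows everyone through the full grace period. The reverse order is equally free of refill conditioning. Keep the grace rule for persistence, compute the discontinuation date from the sequential end of supply, and report the 5000 person-years under the symmetric rule.

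The cost is re-deriving the exposure dataset, plus a trade-off in person-time that the documents do not allow to be fixed. The first-run-out rule can be expensive. In the assumed pattern of 30-day fills, 20% late and gaps uniform from 1 to 60 days, 0.20 × 53/59 = 18% of fills would end follow-up. That is an average of about 1/0.18 = 5.6 fills, or roughly 167 days, if nothing else ended it. Dropping the later gap days with re-entry at the refill loses less in the simulation (677,800 against 778,239 person-years, 13% fewer), but complicates the Kaplan–Meier estimates. The full-grace rule loses none (812,057 person-years), but counts days without supply as treated, which would dilute the bleeding rate if risk falls off drug; the constant-hazard simulation cannot show this. The choice should be fixed before outcomes are examined.

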### Clinical outcomes

2.5

Study measures, including outcomes, are defined using diagnosis, procedure, and medication codes in the formats used in each database; full definitions are presented in Table S1.

To ensure sufficient precision, clinical outcomes for all study populations will only be analyzed if the a priori threshold of 5000 person‐years on‐treatment with ticagrelor 60 mg is met in the Primary population, as a total across all data sources.

The primary outcome, bleeding requiring hospitalization, is defined as an inpatient admission with at least one overnight stay with a primary diagnosis of bleeding. In a sensitivity analysis, the primary bleeding outcome is defined as bleeding events associated with an inpatient admission of ≥2 overnight stays. Additional bleeding outcomes include the individual components of the primary outcome (hospitalization for intracranial hemorrhage, gastrointestinal bleeding and other bleeding, respectively), bleeding episodes not requiring hospitalization, and fatal bleeding.

Outcomes were identified on the event date recorded in the EHD; for composite outcomes, the earliest date of any of the components was used to define the event date. The secondary CV composite outcome is defined as the composite of hospitalization for MI or stroke, and all‐cause mortality. Additional outcomes include the individual components of the secondary CV composite outcome, three‐point MACE (composite of hospitalization for MI or stroke, and CV death), hospitalization for ischemic stroke, CV death, as well as coronary heart disease (CHD) death. To ensure harmonized definitions across all databases, fatal bleeding, CHD death, and CV disease (CVD) death are defined as death within 28 days of an inpatient hospital admission with a primary diagnosis of bleeding, CHD, and CVD, respectively. Sensitivity analyses for these outcomes will be performed in databases reporting cause of death from death certificates (UK and Sweden). Exploratory outcomes include dyspnea and lower‐limb amputation, as well as bleeding requiring transfusion (only available in the US databases).

Due to insufficiently detailed clinical data in all databases to adequately adjust for imbalances in clinical characteristics between cohorts for comparative analyses, clinical outcomes will only be analyzed in the ticagrelor 60 mg cohorts (i.e., not in the reference cohorts).

Subgroup analyses of interest are described in Figure 2.

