### Sample size estimation

2.8

No power calculations were performed as all objectives are descriptive in nature. The a priori threshold of 5000 person‐years on‐treatment for outcomes analyses among patients treated with ticagrelor 60 mg was based on an assumed event rate for bleeding requiring hospitalization of 0.5 per 100 person‐years (the annualized major bleeding rate was approximately 0.9% in the PEGASUS‐TIMI 54 trial).^17^ With a sample size of 5000 patients (assuming an average of 1 year on treatment), the 95% CI would be 0.3–0.7 events per 100 person‐years. The event rate for MACE (hospitalization for MI, stroke, or CV death) was expected to be approximately 2.5 per 100 person‐years (the annualized rate for this outcome was approximately 2.7% in the PEGASUS‐TIMI 54 trial).^17^, ^20^ Given that this outcome is expected to occur more frequently than bleeding requiring hospitalization, the threshold of 5000 person‐years will be applied for all clinical outcome analyses.

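### As written, the primary bleeding outcome leaves out patients who die on the day of admission, because it requires an overnight stay and makes no exception for death

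*Protocol article*

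**What the plan says.** All the definitions are in section 2.5, Clinical outcomes, of the protocol article.

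- **Primary outcome.** Bleeding requiring hospitalization "is defined as an inpatient admission with at least one overnight stay with a primary diagnosis of bleeding".
- **Sensitivity definition.** Here "the primary bleeding outcome is defined as bleeding events associated with an inpatient admission of ≥2 overnight stays".
- **Fatal bleeding.** This is grouped with two other mortality outcomes, which "are defined as death within 28 days of an inpatient hospital admission with a primary diagnosis of bleeding, CHD, and CVD, respectively". No minimum stay is mentioned. It is listed among the additional outcomes, next to the components of the primary outcome and not as one of them: "bleeding episodes not requiring hospitalization, and fatal bleeding".
- **Detail held elsewhere.** The section adds that "full definitions are presented in Table S1". That table is not available here.

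Two other sections decide what happens to a patient who dies without a primary event. Section 2.4 makes the date of death one of the dates that can end treatment. Section 2.7 censors the main outcome analyses when treatment ends.

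**The concern.** A minimum stay is a reasonable way to keep minor or administrative admissions out of a claims-based bleeding outcome. Used alone, however, it also requires the patient to survive until the stay is long enough. A patient admitted with an intracranial bleed who dies that day has no overnight stay for the same reason that the bleed is among the most severe.

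At stake is the study's primary clinical outcome. Events would be missed from the overall bleeding rate, from the intracranial component, and from the Cox models of bleeding risk factors, and the missed events would be those that killed fastest. The only stated check on length of stay raises the threshold, so it cannot reveal the loss.

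**Working it through.** **Step 1. Apply the definitions, as worded, to four patients admitted with a primary diagnosis of bleeding.**

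| Course after admission | Nights | Primary (at least 1 night) | Sensitivity (at least 2 nights) | Fatal bleeding (death within 28 days) |
|---|---|---|---|---|
| Dies the same day | 0 | No | No | Yes, if death is recorded |
| Dies after one night | 1 | Yes | No | Yes, if death is recorded |
| Dies after two nights | 2 | Yes | Yes | Yes, if death is recorded |
| Discharged alive after one night, survives 28 days | 1 | Yes | No | No |

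The first row is the problem in the main definition. The second row shows that the stricter definition adds a further group of deaths to those already left out.

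**Step 2. Follow the first patient through the analysis.** Death ends treatment (section 2.4), and the on-treatment analysis censors at that point (section 2.7). The patient leaves the primary analysis on the day of the bleeding admission, censored and without a bleeding event.

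**Step 3. Reproduce the plan's precision figure.** Inputs from section 2.8: 0.5 events per 100 person-years and 5000 person-years.

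- Expected events: 0.005 × 5000 = 25.
- Wald 95% CI: 0.5 ± 1.96 × √25 / 5000 × 100 = 0.5 ± 0.196, or 0.304 to 0.696 per 100 person-years.
- An exact Poisson interval is 0.324 to 0.738.

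Both round to the stated 0.3–0.7.

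**Step 4. Size the loss.** The article gives no share of bleeding admissions that end in death before the first night, so every input here is an assumption.

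- All bleeding: 5–10% of admissions fatal, 10–30% of those deaths on the admission day. The share f left out is 0.05 × 0.10 = 0.5% to 0.10 × 0.30 = 3%.
- Intracranial bleeding: 30–40% fatal, 20% of those on the admission day. The share is 0.30 × 0.20 = 6% to 0.40 × 0.20 = 8%.

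If 25 events are counted, the number with the missed ones restored is 25 / (1 − f):

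| f | Events with exception | Events missed | Rate per 100 person-years | Understatement |
|---|---|---|---|---|
| 0.5% | 25.13 | 0.13 | 0.503 | 0.003 |
| 3% | 25.77 | 0.77 | 0.515 | 0.015 |
| 10% (stress case) | 27.78 | 2.78 | 0.556 | 0.056 |

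All three are well inside the CI half-width of about 0.2.

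**Step 5. Check where the exception could be applied.** From Table 3, Medicare, the UK, Sweden, Germany and Italy supply 3100 + 250 + 800 + 150 + 1000 = 5300 of 7250 projected patients (73%). All five record deaths that occur in hospital; Italy lacks only deaths outside it. Optum and MarketScan supply 750 + 1200 = 1950 (27%), and the article says their mortality data are not comprehensive.

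**The case against.** The strongest reply is that the detail may already be settled. Outcomes are coded separately for each database, Table S1 holds the full definitions, and the handling of admissions that end in death is the kind of rule such a table would contain. The point is therefore conditional on Table S1. It does not disappear, because the article states the primary definition in full and that wording excludes these patients.

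Several stronger readings are tempting but not supported:

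- **That the two definitions contradict each other.** Nothing in the article says fatal bleeding must be a subset of the primary outcome. It is listed separately, so the mismatch breaks no stated rule. That fatal bleeding carries no stay condition is also read from silence.
- **That the 2-night analysis is meant to isolate severe bleeds and so works backwards.** The article gives no purpose for it. All that can be said is that it also drops deaths after one night.
- **That these deaths are lost to the study.** Where death is recorded they appear in fatal bleeding, in all-cause mortality and in the secondary CV composite. They are missing from the primary outcome and its components.
- **That a treatment comparison is biased.** Clinical outcomes are analysed only in the ticagrelor 60 mg cohorts, so there is no between-cohort outcome comparison to bias.

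It is also fair to object that an exception for death has a cost: it could make ascertainment uneven across databases that are later pooled. That stands, and the fix has to deal with it.

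**Conclusion.** The point holds for the wording of section 2.5, subject to Table S1. Followed literally, a same-day fatal bleed is censored without a primary event, and the 2-night definition extends the exclusion to deaths after one night.

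The effect on the headline rate is probably small: about 0.1 to 0.8 events missed alongside 25 counted, if 0.5–3% of bleeding admissions are affected. No document figure supports that range, and even a 10% share would move the rate by only about 0.06 per 100 person-years. The case for a change therefore rests on the kind of event that is missed. The loss can only lower the rate, it falls on the most severe events, and it is relatively larger for the intracranial component (6–8% of admissions under the assumptions above). Section 2.7 describes only timepoints with at least five events, so a component with few events can be affected by the loss of one.

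Fatal bleeding here means any death within 28 days of a bleeding admission, so the bleed is presumed, not shown, to be the cause.

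**What to change.** First check Table S1. If it already counts bleeding admissions that end in death, add one sentence to section 2.5 saying so.

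Otherwise, amend both definitions so that an admission with a primary diagnosis of bleeding is an event if it reaches the required number of nights or ends in death before reaching it:

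- main definition: at least one night, or death before the first night;
- sensitivity definition: at least two nights, or death before the second night.

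The second clause needs its own wording. Carrying over an exception limited to death before the first night would still leave out patients who die after one night.

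The cost is one clause and one extra condition in the outcome code for each definition. The downside is uneven application in Optum and MarketScan, where death capture is not comprehensive. To make that visible, report the primary outcome with and without the exception, and repeat both in the meta-analysis already planned without those two databases.

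The change does not make fatal bleeding a strict subset of the primary outcome. A patient discharged alive before the required nights who dies within 28 days would still count only as fatal bleeding. The aim is narrower: to stop the length-of-stay rule from excluding a bleed because the patient died.
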